## Aims and objectives

This study aims to evaluate the quality of care, acceptability, effectiveness and cost-effectiveness of the CDCC Pilot Scheme. The objectives of this study are to:

Measure the adherence to the standards of care criteria by healthcare providers participating in the Scheme;Evaluate participant acceptability by self-reported outcomes on enablement, experience and satisfaction level about the services of the Scheme;Evaluate the effectiveness of the Scheme in improving health outcomes among CDCC participants over 12 months; and.Determine the provider costs and cost-effectiveness for delivering the CDCC Pilot Scheme relative to its effectiveness on participants health outcomes.

We hypothesize that:

Healthcare providers participating in the Scheme would achieve over 70% adherence for the standards of care criteria;60% of participants will report an increase in patient enablement levels after 12 months;90% of participants will report patient satisfaction 12 months after enrolment;A greater proportion of participants in the CDCC Pilot Scheme would achieve targets for disease control outcomes after 12 months compared to the comparison group; and.The Scheme would be cost-effective based on an incremental cost-effectiveness ratio (ICER) lower than the willingness-to-pay threshold of 1 annual gross domestic product (GDP) per person.

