### Sample size calculation

The sample size needed for evaluating participant acceptability is based on the proportion of participants who showed an increase in enablement, measured by the Patient Enablement Instrument (PEI), one year after enrolment into the CDCC Pilot Scheme. Previous studies showed that 55.6–72.2% of participants reported PEI score > 0 after entering structured programmes for DM and/or HT [10–12]. Assuming the proportion of CDCC participants with PEI score > 0 at 12 months to be 50%, 383 CDCC participants are required with 5% margin of error and significance level of 5%. To allow for about 30% attrition, the sample size required will be 548.

The sample size for evaluating the effectiveness and cost-effectiveness was determined based on the difference in the proportion of patients achieving the targeted outcome for disease control after 12 months between CDCC participants and the comparison group. Previous studies evaluating the 12-month effectiveness of the multi-disciplinary Risk Assessment and Management Program for DM or HT implemented in public primary care in Hong Kong found that the proportion of participants achieving treatment target (glycated hemoglobin [HbA1c] < 7.0% or systolic/diastolic blood pressure [BP] < 140/90mmHg) increased by 5.40% [13] or 1.18% [14], respectively after 12 months, compared to patients receiving usual care. Assuming a conservative 3% increase in the proportion of participants achieving treatment target after 12 months in the CDCC group, a total of 378 participants with pre-DM, HT and/or DM are required to detect difference at a power of 80% with a significance level of 5%/ According to the Hong Kong Population Health Survey 2020, the prevalence of undiagnosed HT and DM among individuals aged 45–84 was 15.4% and 4.6%, respectively [15]. Previous studies reported that the prevalence of pre-DM was 2.3–8.9% in Hong Kong [15, 16]. Taking a prevalence of approximately 20% in total for pre-DM, HT and/or DM, and accounting for an attrition of 30%, a total of 1,886 non CDCC participants will be required.

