### Outcome measures

#### Primary

The proportion of participants and service providers achieving each criterion of the evaluation framework.Participant enablement measured by the PEI at 3 and 12 months.Differences in the proportion of CDCC and non-CDCC participants achieving the targeted disease control outcome after 12 months (systolic/diastolic BP < 140/90mmHg for HT, reduced HbA1c for pre-DM, HbA1c < 7% for DM).Differences in health service utilization rate and direct medical costs of CDCC and non-CDCC participants within 12 months from enrolment.The ICER for achieving the targeted outcomes for disease control.

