### Data analysis

The proportion of patients and/or service providers achieving the standards of care, participant experience, satisfaction and enablement, and the costs of the CDCC Pilot Scheme and the direct medical costs from the participants at 12 months will be described with descriptive statistics. Differences in the proportion of participants reaching the targeted disease control outcomes between CDCC and non-CDCC participants will be compared using chi-squared tests, and adjusted for confounding factors by logistic regression. Changes in clinical parameters from baseline to 12 months will be compared between CDCC and non-CDCC participants by paired t-tests. The total mean costs on each CDCC and non-CDCC participant will be compared using t-tests. The additional costs required for an additional participant in the CDCC Pilot Scheme to achieve target outcomes of disease control after 12 months will be reported as the ICER, calculated as the incremental cost incurred for each participant of the CDCC Pilot Scheme divided by the difference in the proportion of participants meeting targeted disease outcome. Cost-effectiveness of the Scheme would be determined by comparing the ICER to the willing-to-pay threshold of 1 GDP per year.

All statistical analyses will be performed using Stata (version 15.1). A p-value < 0.05 is considered statistically significant.

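### The fifth hypothesis calls the Scheme cost-effective if the cost per additional participant at target is below 1 GDP per person, but nothing in the plan ties that threshold to this unit of effect

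*Protocol article*

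**What the plan says.** The protocol article settles three things itself.

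- **The ratio.** Data analysis defines the ICER as "calculated as the incremental cost incurred for each participant of the CDCC Pilot Scheme divided by the difference in the proportion of participants meeting targeted" (the quotation stops just short of the words naming the target). Outcome measures (Primary) lists it as a primary outcome: "The ICER for achieving the targeted outcomes for disease control".
- **The effect unit.** The same list of primary outcomes defines the target by diagnosis: "systolic/diastolic BP < 140/90mmHg for HT, reduced HbA1c for pre-DM, HbA1c < 7% for DM".
- **The decision rule.** Data analysis states: "Cost-effectiveness of the Scheme would be determined by comparing the ICER to the willing-to-pay threshold of 1 GDP per year". Aims and objectives makes this the last of five hypotheses: the Scheme is expected to have an "incremental cost-effectiveness ratio (ICER) lower than the willingness-to-pay threshold of 1 annual gross domestic product (GDP) per person".

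The two statements of the threshold differ slightly, because Data analysis leaves out the words that make it a per-person figure. The check below uses the per-person reading from Aims and objectives.

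**The concern.** A willingness-to-pay threshold says how much one unit of effect is worth, so it needs a stated unit. The ICER here is money per additional participant at target. The threshold is an annual GDP per person, with nothing said about what that sum buys. For the comparison to support a conclusion of value for money, the plan would need either a reason why one more participant at target is worth that sum, or a route from target attainment to a unit in which the sum is defended. The article gives neither.

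The effect unit is also not uniform. Reaching a blood pressure cut-off, reaching an HbA1c cut-off and showing a reduction in HbA1c each count as one success, so a single price per success needs more justification, not less.

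The Background says the evaluation is meant to inform future primary healthcare planning and policy. A declared verdict of cost-effective for a territory-wide subsidised programme would carry weight, and under this rule it would not follow from the data.

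**Working it through.** The article states no ICER value and no monetary value for GDP, so there is no figure to reproduce. The check is of units, followed by what the rule implies in multiples of per-capita GDP.

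**Inputs**

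- ΔC: incremental cost per participant (Data analysis).
- ΔP: difference in the proportion at target. Sample size calculation plans for 3 points: "Assuming a conservative 3% increase in the proportion of participants achieving treatment target after 12 months in the CDCC group". I read this as an absolute difference. The same section cites two earlier programmes in which the proportion "increased by 5.40% [13] or 1.18% [14], respectively after 12 months".
- Threshold: 1 GDP per person (Aims and objectives).
- q: QALYs represented by one additional participant at target. This is **not in the documents**; values from 0.01 to 1 are assumed to show the range.

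**Step 1: units.** ICER = ΔC / ΔP, which is money per additional participant at target. The threshold is money, per person and per year, with no effect unit. The comparison has a meaning only if the threshold is taken as the price of one additional participant at target. The article neither says nor defends this.

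**Step 2: what the rule passes if taken literally.** For ΔP > 0, ΔC / ΔP < 1 GDP is the same as ΔC < ΔP × 1 GDP.

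| ΔP | Incremental cost per participant must be below |
|---|---|
| 0.0118 | 0.0118 GDP per person |
| 0.03 (planned) | 0.03 GDP per person |
| 0.054 | 0.054 GDP per person |

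At the planned effect, any incremental cost below 3% of per-capita GDP per participant passes.

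**Step 3: what an ICER of exactly 1 GDP means per QALY.** Cost per QALY = ICER / q = 1/q GDP.

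| Assumed q | GDP per QALY |
|---|---|
| 1 | 1 |
| 0.5 | 2 |
| 0.1 | 10 |
| 0.05 | 20 |
| 0.01 | 100 |

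The same ICER therefore covers a hundredfold range, and the article offers nothing to place the Scheme within it.

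**Step 4: precision of the denominator, which affects the remedy.** The 95% half-width for ΔP is 1.96 × √{[p₁(1−p₁) + p₂(1−p₂)] / n}. I assume n = 378 per group (the article gives 378 as a total) and 50% or 90% at target in the comparison group; neither assumption is stated in the article.

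- 50% vs 53%: 1.96 × √[(0.2500 + 0.2491)/378] = 0.071, or 7.1 points.
- 90% vs 93%: 1.96 × √[(0.0900 + 0.0651)/378] = 0.040, or 4.0 points.

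Both exceed 3 points, so an interval centred on the planned effect would include zero. An ordinary confidence interval for ΔC / ΔP may then be undefined.

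**The case against.** The strongest reply is that the comparison can be computed. With no health-effect unit attached, the threshold can be read as a willingness to pay up to one annual GDP per person for one more participant at target, and both sides are then money per additional participant. This stands. A reader might infer that the plan sets a ratio per participant at target against a threshold per year of life or health, so that the units conflict outright. The documents do not support that, because they never say the threshold is per life-year or per QALY. What remains is that the threshold is unjustified for the unit to which it is applied.

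A reader might also infer that the rule is lenient by a factor of 10 to 100. That figure comes entirely from assuming q between 0.01 and 0.10, which nothing in the documents supports. One could argue that a person cannot gain more than one QALY in 12 months, so the rule is never stricter than 1 GDP per QALY over the observed year. But that bound holds only if all the health gain comes through the extra participants at target, and it ignores later gains. Without a model, neither the size nor the direction is established.

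It is also fair that the absence of a minimum HbA1c reduction for pre-diabetes concerns the endpoint definition. An article may leave that to the full protocol, so it adds nothing to the seriousness of this point. Finally, the ICER itself is a legitimate descriptive result, and the Abstract presents it only as an indicator. The fault is confined to one hypothesis and one sentence of the analysis section.

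The reply does not make this a detail left to an unseen plan. The article itself fixes the denominator, the threshold and the rule that joins them.

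**Conclusion.** The concern holds: the pass/fail verdict in the fifth hypothesis is unsupported. The article prices one additional participant at target at 1 GDP per person without giving the threshold an effect unit, a conversion or a justification. Meeting the rule would therefore not show value for money, and missing it would not show the reverse.

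The one size that follows from the article's own figures is the ceiling of 3% of per-capita GDP per participant at the planned 3-point effect. That figure does not by itself show the rule to be too generous. In QALY terms the rule corresponds to 1/q GDP per QALY. Since q is unknown, so is the size of any leniency. The conclusion does not depend on any value of q, and nothing here questions reporting the ICER itself.

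**What to change.** Remove the comparison with 1 GDP from the fifth hypothesis and from Data analysis. Report the incremental cost per participant, the difference in the proportion at target, and the cost per additional participant at target as descriptive results.

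Show uncertainty through the joint bootstrap distribution of incremental cost and effect, or an acceptability curve over a range of willingness to pay per additional participant at target. Do not rely on a plain 95% interval for the ratio, because the denominator may not be distinguishable from zero.

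If a verdict is wanted, there are two sound routes:

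- pre-specify a conversion from target attainment to QALYs or life-years, and apply 1 GDP per person to the resulting cost per QALY or life-year; or
- state and justify a threshold in the target-attainment unit.

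Whichever threshold is kept, word it identically in both sections, including whether it is per person.

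The basic change rewords one hypothesis and one analysis sentence, adds a modest joint uncertainty analysis of cost and outcome data already planned, and needs no new data collection. The sponsor gives up the yes/no verdict unless it takes on the modelling or the justification.

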## Discussion

The CDCC Pilot Scheme is a territory-wide programme to advocate early screening and management of chronic diseases with private-public partnership in the community setting. The implementation of the Scheme involves various stakeholders including the Primary Healthcare Commission, DHC/DHC Express, FDs and allied health professionals. A timely evaluation of the Scheme at this pilot stage is needed to assure the cross-sector collaboration works as expected and to inform strategies for quality enhancement in the future. Guided by the three domains of quality of care (structure, process and outcome), key stakeholders were involved at the initial phase to develop the evaluation criteria and standards, incorporating feedback from service providers based on real-world practice. The inclusion of various stakeholders and providers, and adoption of both subjective (self-reported outcomes) and objective (site visits and health parameters) data collection methods enhance the validity and reliability of the results. Results of the evaluation could shed light on good practices that has already been adopted and inform future guidelines to improve service quality.

Previous evaluation studies on the Risk Assessment and Management Program in Hong Kong, a chronic disease management programme implemented in public primary care, discussed approaches to facilitate the evaluation of multi-disciplinary programme [26]. They include coordinating stakeholder collaboration and communication, continuous feedback and planning meetings, stakeholder endorsement and validation, development of evaluation framework and operation definitions, and ensuring data quality. These recommendations have been incorporated in the current evaluation.

The CDCC Pilot Scheme was officially launched in the November 2023. To date, the evaluation framework has been developed, and have already conducted all site visits to DHC/DHC Express. The recruitment of participants for the participant experience and enablement survey and control group non-participants are in progress. We anticipate the major challenges in the evaluation to be:

Stakeholder endorsement and validation.

Standard operation protocols have been established by the Primary Healthcare Commission to specify the standards of operation for DHC/DHC Express and FDs. Since the DHC/DHC Express varied in scale, resources available, and located across districts, slight variations in real-world practice among centers is expected. For instance, staff availability, capacity of the centre, and the number of participants recruited can influence the mode of service delivery. It is essential to understand these potential variations in daily operational practices through site visits and to collectively explore solutions. Core criteria for ensuring standardized care are delivered across centers should be identified, and adherence to such criteria is non-negotiable. Alternatively, criteria that enhances patient care but are outside of the core criteria may effectively inform practices that would improve quality of care once resources become available.

2.Development of evaluation framework and operation definitions.

The indicators and standards of the evaluation framework are derived from standard operation protocols derived by the Primary Healthcare Commission for various service providers. To facilitate comprehension and interpretation of the framework, operation definitions have been developed for the framework, as well as specifying the service providers applicable for each indicator, and the corresponding source of data (site visit, questionnaire or data extraction) in order to ease data collection.

3.Ensuring data quality.

The data of the CDCC Pilot Scheme are captured in multiple IT modules and managed by the Primary Healthcare Commission. Since a range of personnel from different service providers can input and access participant data through the IT modules, monitoring data quality is of utmost importance for a valid and reliable evaluation. To achieve this, we have worked closely with the Commission to align our understanding of the data fields and their definitions. Several issues observed to date have included (i) incomplete data entry such as laboratory records, missing attendances and treatment plans, (ii) missing diagnoses of participants who are lost to follow-up after the initial screening phase, and (iii) missing consultation records by FDs who encounter difficulties using the IT system. To overcome these challenges, through discussion with the Commission and service operators, (i) participants' diagnosis will be defined by the latest treatment plan, the latest laboratory record will be used for evaluating effectiveness. Staff at DHC/DHC Express will also (ii) follow up with the FDs on the missing diagnosis and (iii) provide guidance on the system interface to the FDs who are in need.

Maintaining close collaboration and communication with stakeholders is the key to implementing this evaluation study. We shall gather their feedback through regular meetings and address the concerns from different parties, including the expectation of the health policymakers, the progress of deliverables achievement by service operators, and the practical difficulties encountered by frontline staff. The goal of this evaluation study is to consolidate the issues that arose in practice and advise on feasible solutions upon discussion with relevant stakeholders, with the aim of enhancing the capacity of providers to offer quality care and raise participant satisfaction. Results from this evaluation would provide practical and specific recommendations to inform optimal delivery of the CDCC Pilot Scheme, while the processes used to develop this evaluation can be easily adapted for similar cross-sector screening and management programme in the community to improve the delivery of primary healthcare services.

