#### Evaluation of the effectiveness and cost-effectiveness

Anonymous data including demographics, diagnoses, prescriptions and laboratory tests (e.g. full lipid profile and renal function test) at baseline and 12 months for CDCC participants will be extracted from the eHealth database and DHC IT module, whereas those for non-CDCC participants will be collected via a telephone survey by an independent professional survey provider, and they will complete the screening blood test at a designated laboratory. With the exception of critical results that requires immediate medical attention, participants of the comparison group will be asked to follow up on any abnormal results on their own.

Costs of the CDCC Pilot Scheme composes the of implementation and operation costs by health service providers and the direct medical costs of participants. The total costs of implementing CDCC services will include all expenditure incurred from setting up the programme until 31 Dec 2024, while ongoing operational costs would be collected over a 1-year period from Dec 2023– Dec 2024 (Appendix C). Costs will be collected from each DHC/DHC Express, a representative sample of service providers and the Primary Healthcare Commission at 12 months using a costing questionnaire.

Direct medical costs refer to the ongoing costs on utilization of public and private healthcare services (including hospitalization, Accident & Emergency department, General Out-patient Clinics, and Specialist Out-patient Clinics) for both CDCC and non-CDCC participants, as well as the co-payment for the CDCC services among CDCC participants, within 12 months from enrolment. The information will be extracted anonymously from the Hospital Authority’s eHealth database and Clinical Management System, and collected from participants through telephone survey at 12 months (Appendix D). The cost of public healthcare service utilization will be estimated by multiplying the frequency of utilization with the unit cost published in the Gazette and Hospital Authority ordinance (Chap. 113) of charges for non-entitled persons for each public healthcare service.

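### Taking CDCC diagnosis from the latest treatment plan and HbA1c from the latest laboratory record lets post-enrolment care decide who is counted, which target applies and when the outcome is read

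*Protocol article*

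**What the plan says.** The rule stands in the Protocol article, Discussion, third challenge (ensuring data quality). In answer to gaps in the Scheme's IT data, a participant's "diagnosis will be defined by the latest treatment plan, the latest laboratory record will be used for evaluating effectiveness". The gaps listed just before it include "incomplete data entry such as laboratory records, missing attendances and treatment plans" and "missing diagnoses of participants who are lost to follow-up after the initial screening phase". The same paragraph adds that centre staff will follow up missing diagnoses with the family doctors.

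The primary effectiveness outcome (Outcome measures, Primary) is "Differences in the proportion of CDCC and non-CDCC participants achieving the targeted disease control outcome after 12 months", with the target set by diagnosis: "systolic/diastolic BP < 140/90mmHg for HT, reduced HbA1c for pre-DM, HbA1c < 7% for DM".

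The section on evaluating effectiveness and cost-effectiveness says that data "at baseline and 12 months for CDCC participants will be extracted from the eHealth database and DHC IT module", while "those for non-CDCC participants will be collected via a telephone survey by an independent professional survey provider", and that "they will complete the screening blood test at a designated laboratory". Comparators are left to follow up abnormal results themselves, unless a result is critical. The article does not say how a comparator's diagnosis is fixed.

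Under Data analysis, the proportions at target are compared by chi-squared test and by logistic regression with adjustment for confounders. The difference in proportions is also the denominator of the ICER.

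**The concern.** In a comparison of disease control, the set of people counted and the criterion each must meet should be settled at entry, in the same way in both groups. Here, on the CDCC side, both come from a document that exists only if the participant stays in contact with Scheme care, and that can be revised as the participant's condition changes. The HbA1c value comes from whichever record happens to be last.

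At stake are two primary outcomes: the difference in the proportion at target, and the ICER that is divided by it. The planned difference is only 3 points, so a modest distortion matters. Covariate adjustment does not help, because a regression cannot recover people who were never entered or undo a change of target.

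**Working it through.** The plan gives no figure for this bias, so there is none to reproduce. The 3-point increase assumed under Sample size calculation serves only as a yardstick.

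**1. Who is counted.** The target is defined by diagnosis, and diagnosis by the latest treatment plan. A CDCC participant with abnormal screening results and no plan therefore has no diagnosis and no target under the rule. Suppose a fraction f is lost in this way, and those lost reach target g points less often than those kept. The proportion among those kept is then too high by f × g. The bias in the difference between groups is net of the comparators' own loss:

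net bias = f(CDCC) × g(CDCC) − f(comparator) × g(comparator)

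The article gives none of these four quantities. Under assumed losses, the rise in one group's proportion is:

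| Lost: non-achievers / achievers | True rate 50% | 60% | 70% |
|---|---|---|---|
| 10% / 5% | 1.4 points | 1.3 | 1.1 |
| 20% / 10% | 2.9 | 2.8 | 2.4 |
| 30% / 20% | 3.3 | 3.2 | 2.7 |

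For the middle row at 50%: kept achievers 0.50 × 0.90 = 0.45, kept non-achievers 0.50 × 0.80 = 0.40, and 0.45 / 0.85 = 52.9%. If comparators lose people in the same pattern, the net bias is 0. At a true rate of 50%, if CDCC follows the middle row and comparators the top row, it is 2.94 − 1.35 = 1.6 points in favour of CDCC. With the rows swapped it is 1.6 points against.

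**2. Which target applies.** Take a participant classed pre-DM at screening whose HbA1c rises to 6.7% and whose latest plan says DM. Against the pre-DM target (a reduction) this is a failure. Against the DM target (below 7%) it is a success. If screening HbA1c was below 7%, a change of label from pre-DM to DM can only help: a participant whose HbA1c fell passes either way, and one at 7% or above fails either way.

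For size, the prevalences under Sample size calculation are 15.4% for undiagnosed HT, 4.6% for undiagnosed DM and 2.3–8.9% for pre-DM. Ignoring overlap, pre-DM makes up 2.3 / 22.3 = 10% to 8.9 / 28.9 = 31% of cases. If 10% of pre-DM cases move from fail to pass (assumed; the article gives no relabelling rate), the CDCC proportion rises by 0.10 × 10% = 1 point to 0.10 × 31% = 3 points.

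**3. When the outcome is read.** The outcome is meant for 12 months, but latest has no window. If no repeat test was entered, the latest record is the screening record. A DM participant already below 7% at screening is then a success with no follow-up, and a pre-DM participant shows no reduction and fails. The direction is therefore open. BP is not a laboratory record, so this part does not reach HT, which on the same prevalences is 15.4 / 28.9 = 53% to 15.4 / 22.3 = 69% of cases.

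**Carry-over to the ICER.** At unchanged cost, if a true difference of 3 points is inflated by 1 point, the ICER falls to 3/4 of its value. If it is inflated by 3 points, the ICER falls to half.

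**The case against.** The strongest reply is that this is a remark on data quality in the Discussion, while the outcome and data-collection sections name baseline and 12 months. Latest may mean only a choice among several records, with the window left to the analysis plan. That is a fair reading of intent. But the sentence is a stated rule for the effectiveness evaluation, it has no date limit, and it ties diagnosis to the plan rather than to screening. The reading that respects 12 months still leaves the first two effects in place.

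Several further objections stand and limit the point:

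- Staff will chase missing diagnoses. This reduces the loss from the denominator but need not remove it, and it does nothing about relabelling or dates.
- A reader might infer that comparators are classified at baseline and all stay in. The article does not say so. Their diagnoses may also be updated at follow-up, and losses among them are expected. All that follows is that a rule based on a Scheme treatment plan cannot be applied to people who have none.
- A reader might apply the plan's 30% attrition to CDCC records and, with an assumed 10-point gap, arrive at 0.30 × 10 = 3 points, the whole planned effect. That 30% belongs to the acceptability survey and to the non-CDCC sample, not to CDCC records, and the product ignores offsetting loss among comparators.
- Relabelling helps only pre-DM participants whose HbA1c did not fall, who are relabelled DM and who stay below 7%. This may be a small group.

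**Conclusion.** The point holds as a fault in a stated rule. Followed literally, it makes the CDCC denominator, the choice between the pre-DM and DM targets, and the date of the HbA1c outcome depend on care after enrolment, and the rule has no counterpart in the comparison group. Relabelling from pre-DM to DM favours the Scheme, given a screening HbA1c below 7%. Selective loss would favour the Scheme only if it is heavier or more selective in CDCC than among comparators. The date effect can go either way.

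The net size cannot be derived from the article. The figures of about 1 to 3 points for relabelling, and those in the table for loss, rest on assumed rates. They show only that plausible inputs are comparable with the 3-point planned effect. They do not show that a positive result would be an artefact. Because the rule feeds two primary outcomes, it should be settled before the comparison is run.

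**What to change.** For the CDCC versus non-CDCC comparison and the ICER:

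- Classify participants in both groups from their baseline screening results with the same criteria, and keep that class and its target fixed to the end.
- For HT, use the baseline BP information available in each group and state any difference in source. The article describes a telephone survey and a blood test for comparators but no measured BP, so it is not shown that comparable records are already held.
- Include every screen-positive participant, whether or not a treatment plan exists.
- Use the record closest to 12 months within one prespecified window, the same for both groups.
- Treat no record in the window as missing, for example by multiple imputation, with not at target as a sensitivity analysis. Never fill the gap with the screening value.

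The latest-plan and latest-record rule can stay for the quality-of-care part.

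The cost is mainly in extraction rules and analysis wording, with some extra analysis work and, for HT, a check of what BP information exists for comparators. The CDCC result may look less favourable.
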